# Protocol for the CONVERT trial—Concurrent ONce-daily VErsus twice-daily RadioTherapy: an international 2-arm randomised controlled trial of concurrent chemoradiotherapy comparing twice-daily and once-daily radiotherapy schedules in patients with limited stage small cell lung cancer (LS-SCLC) and good performance status

**DOI:** 10.1136/bmjopen-2015-009849

**Published:** 2016-01-20

**Keywords:** CHEMOTHERAPY

## Abstract

**Introduction:**

Concurrent ONce-daily VErsus twice-daily RadioTherapy (CONVERT) is the only multicentre, international, randomised, phase III trial open in Europe and Canada looking at optimisation of chemoradiotherapy (RT) in limited stage small cell lung cancer (LS-SCLC). Following on from the Turrisi trial of once-daily versus twice-daily (BD) concurrent chemoradiotherapy, there is a real need for a new phase III trial using modern conformal RT techniques and investigating higher once-daily radiation dose. This trial has the potential to define a new standard chemo-RT regimen for patients with LS-SCLC and good performance status.

**Ethics and dissemination:**

The trial received ethical approval from NRES Committee North West—Greater Manchester Central (07/H1008/229). There is a trial steering committee, including independent members and an independent data monitoring committee. Results will be published in a peer-reviewed journal and presented at international conferences.

**Trial registration number:**

ISRCTN91927162; Pre-results.

Strengths and limitations of this studyThis is an adequately powered multicentre, randomised controlled trial aiming to establish a standard chemoradiotherapy regime in limited stage small cell lung cancer.All patients are treated with modern radiotherapy. This trial uses and reflects the important developments in modern conformal radiotherapy techniques that have taken place in the past 20 years.Elderly patients are not excluded. Inclusion/exclusion criteria are based on good performance status with no upper age restriction.

## Introduction

Of the 42 000 patients diagnosed with lung cancer each year in Britain, 15% will have small cell lung cancer (SCLC) and 30% of those patients will have limited stage (LS) disease that can be encompassed within a tolerable radiation therapy field. Outcome is poor even in this early stage of disease, with a median survival of 16–24 months, using current forms of treatment.^1–3^ Combining chemotherapy and thoracic radiotherapy (RT) is the standard treatment for LS SCLC). Two meta-analyses have shown that RT associated with chemotherapy improves median survival, 3-year survival rate and local control.^4^
^5^ Subsequently, meta-analyses of trials investigating the optimal timing and sequencing of chemo-RT have shown that the best results have been reported with early concurrent thoracic RT.^6–9^ Furthermore, it has been demonstrated that twice-daily RT is superior to once-daily RT, in the landmark Turrisi study.^3^ Patients were randomised to either 45 Gy once-daily (1.8 Gy per fraction) over 5 weeks or 45 Gy given twice-daily (1.5 Gy per fraction) over 3 weeks. In both arms, RT was given concurrently starting with the first cycle of chemotherapy (cisplatin and etoposide). Twice-daily RT improved 5-year OS (26% vs 16% in the once-daily arm), reduced the risk of thoracic relapse (52% compared with 36% in the twice-daily arm) but at the cost of increased grade 3 radiation oesophagitis (defined as inability to swallow more than liquids, or to require hospitalisation). However, there were no other significant differences in acute toxicity between the two arms and no long-term oesophageal strictures were reported. Consequently, twice-daily RT concurrently with chemotherapy is accepted as a standard regime in LS-SCLC.^10^ It is, however, unclear whether the better results in the twice-daily arm are explained by the increase in the biologically equivalent dose of radiation in the twice-daily arm or by the use of altered fractionation leading to a shorter overall treatment time. Indeed, the control dose was considered to be quite low, for example, in comparison with the NCI Canada regime of 40 Gy in 15 daily fractions.^1^ Moreover, since the late 1980s, when the Turrisi trial was designed, important progress has been made in RT techniques. The RT used in any contemporary trial should be CT-planned, conformal treatment, with individual field shaping careful dose calculation using modern planning algorithms of target and organs at risk, with image guidance, correction of set-up errors and allowance made for the effects of respiratory motion on the position of the target volume. None of these were routine from 1989–1992, when the Turrisi trial was carried out. The use of three-dimensional RT/intensity modulated RT and the omission of elective nodal irradiation are likely to result in lower rates of toxicity, particularly oesophagitis. Further studies by Choi *et al*,^11^ using once-daily RT, and Komaki *et al*,^12^ using a concomitant boost technique, have suggested that doses of 70 Gy over 7 weeks and 61.8 Gy over 5 weeks, respectively, are possible, the former being delivered in five cycles of full-dose chemotherapy.

There is, therefore, a need to improve on the current survival results, and a strong rationale to compare twice-daily with a higher dose of radiation delivered once-daily.

In view of the lack of data in the literature addressing the question of the dose and fractionation for LS-SCLC, we carried out a randomised phase III trial to establish a standard chemo-RT regimen for LS-SCLC with good performance status (PS) (Concurrent ONce-daily VErsus twice-daily RadioTherapy, CONVERT). At the time the trial was being developed, in 2006–2007, there were no international trials for this group of patients, thus an opportunity existed to set up a global trial to answer this important question. The results of the trial will be crucial in determining the best international standard treatment for routine clinical use in the treatment of patients with limited-stage SCLC and good PS. In addition, the translational studies carried out in parallel with CONVERT will indicate those hypotheses needing testing in the next generation of trials in this disease.

## Methods and analysis

The CONVERT trial is an international, multicentre, prospective, non-blinded, superiority randomised controlled trial. The trial is sponsored by The Christie NHS Foundation Trust and coordinated by the Manchester Academic Health Science Centre Trial Co-ordination Unit (MAHSC-CTU) based at The Christie NHS Foundation Trust. The trial is registered on the International Standardised Randomised Controlled Trial Registry (ISRCTN91927162) and funded by Cancer Research UK's Clinical Trials Awards & Advisory Committee (CTAAC). The study is included in the NIHR Clinical Research Network portfolio (ID: 3823). The trial is conducted in accordance with the Declaration of Helsinki and Good Clinical Practice (GCP).

The primary research question is to establish whether the results of twice-daily chemo-RT for patients with LS-SCLC and good PS can be improved on, by delivering a higher dose of RT once-daily concurrently with chemotherapy. We will compare survival of patients treated with standard chemotherapy (cisplatin and etoposide) and either twice-daily RT or high dose once-daily RT.

The secondary research questions will compare the following factors between the groups receiving either once or twice-daily RT:
Local progression-free survivalMetastasis-free survivalAcute and late toxicity based on the Common Terminology Criteria for Adverse Events V.3.0 (CTCAE V.3.0)^13^Chemotherapy dose intensityRadiotherapy dose intensity.

### Setting

Five hundred and forty-seven patients with a histological or cytological proven diagnosis of SCLC were recruited from 74 centres in eight countries between April 2008 and November 2013 (see online supplementary appendix 1 for details of recruiting centres).

Patients were randomised to receive either concurrent twice-daily RT (45 Gy in 30 twice-daily fractions over 3 weeks, 5 days per week, starting on day 22 of cycle 1) or concurrent once-daily RT (66 Gy in 33 daily fractions over 6.5 weeks, 5 days per week, starting on day 22 of cycle 1). Patients are followed up until death. The study flow diagram is shown in figure 1.

**Figure 1 BMJOPEN2015009849F1:**
[figure not shown]
Trial schema/flowchart. BD, twice-daily; IV, intravenous; OD, once-daily.

### Participant screening and selection

All patients with LS-SCLC with good PS and suitable for concurrent chemo-RT were identified as potential trial candidates. Eligible patients invited to participate were provided with a patient information sheet (see online supplementary appendix 2).

### Inclusion and exclusion criteria

Patients were eligible for the trial if all of the following criteria were met:
Either sex, age ≥18 years.PS Eastern Cooperative Oncology Group grade 0–1. Patients with PS 2 whose general condition is explained by obstructive/bulky disease likely to improve after the first cycle of chemotherapy can be included at the discretion of the local investigator. Patients with PS 2 as a result of comorbid conditions will be excludedHistologically or cytologically confirmed SCLCNo patients with mixed small-cell and non-small-cell histological featuresNo history of previous malignancy in the past 5 years (except non-melanomatous skin or in situ cervix carcinoma). Patients with previous malignancies (except breast cancer) and in remission for at least 5 years can be includedLimited stage disease (Veterans Administration Lung Cancer Study Group), that is, patients whose disease can be encompassed within a radical radiation portalNo pleural or pericardial effusions proven to be malignantRadiotherapy target volume acceptable by the local radiotherapistPulmonary function
Forced expiratory volume in 1 s >1 L or 40% predicted valueTransfer coefficient of the lung for carbon monoxide (KCO) >40% predictedMaximum of one of the following adverse biochemical factors:
Serum alkaline phosphatase more than >1.5 times the upper limit of normalSerum sodium <lower limit of normalSerum lactate dehydrogenase >upper limit of normalNormal serum creatinine and calculated creatinine clearance ≥50 mL/min. If calculated creatinine clearance is <50 mL/mn according to the Cockroft and Gault formula, a glomerular filtration rate should be performedAdequate haematological function
Neutrophils >1.5×10^9^/LPlatelets >100×10^9^/LAdequate liver function: alanine transaminase and aspartate aminotransferase ≤2.5×upper limit normalNo other previous or concomitant illness or treatment that, in the opinion of the clinician, will interfere with the trial treatments or comparisonsNo prior surgical resection of the primary tumour, no prior RT for lung cancer.Considered fit to receive any of the trial regimensFemale patients must satisfy the investigator that they are not pregnant, or are not of childbearing potential, or are using adequate contraception. Men must also use adequate contraceptionPatients must not be breastfeedingPatient has read the patient information sheet and has signed the consent formPatients available for follow-up

### Informed consent

Eligibility to participate was confirmed by a clinician prior to consent being taken. Patients were given at least 24 h to consider the patient information sheet and time to ask questions prior to written informed consent being taken by a trial doctor. The consent form can be viewed in online supplementary appendix 3.

### Randomisation

Randomisation was administered centrally by the MAHSC-CTU. Patients were randomised on a 1:1 basis to one of the two treatment arms. The allocation method used was minimisation with a random element. Randomisation was implemented via a bespoke computer application at the randomisation centre. The factors controlled for in the allocation were institution, planned number of cycles (4 or 6) and PS (0/1 or 2). Randomisation was only performed after confirmation that the patient was eligible (including recording of LDH, sodium and alkaline phosphatase results) and that the patient had signed consent. Randomisation can be undertaken by telephone or fax. The system used did not permit any editing of fields by users after arm allocation had been performed.

### Standard care

Concurrent chemo-RT is the standard of care in LS-SCLC and good PS. The combination of cisplatin and etoposide is the standard chemotherapy treatment delivered concurrently with RT in this group of patients. One of the accepted international standard RT regimes is 45 Gy in 30 fractions delivered twice-daily, the control arm of the CONVERT trial.^3^ However, in reality, RT regimes differ widely between institutions and twice-daily RT has not been adopted widely mainly due to logistical issues.^12^

### Interventions

In both arms, three-dimensional conformal RT was used and 4–10 MV photons emitted from linear accelerators. Thoracic RT was started on cycle 1, day 22, concurrently with the second cycle of chemotherapy, where possible. Intensity modulated RT and positron emission tomography-CT planning were permitted but not mandated. The full trial-specific procedure for RT can be found in online supplementary appendix 4, including the definition of the Planning Target Volume. However, it is important to note that, in this trial, clinically uninvolved lymph node stations were not irradiated.^14^

Patients randomised to the twice-daily thoracic RT arm received 45 Gy in 30 twice-daily fractions over a period of 19 days, five consecutive days a week. The optimal overall treatment time was 19 days. The inter-fraction interval was 6–8 h. Concurrent chemotherapy was administered during the intervals between the two daily RT fractions.

Patients randomised to the high dose once-daily thoracic RT arm received 66 Gy in 33 daily fractions over a period of 45 days, five consecutive days a week. The optimal overall treatment time was 45 days.

Patients received cisplatin and etoposide, for four to six cycles, every 3 weeks, in both arms. Centres were given the choice to stop chemotherapy after four cycles or to continue it up to six cycles. Centres that decided to give six cycles were asked to continue doing so for all patients entered in the trial (unless it was decided that it was not in the patients’ best interest to receive cycle 5 and 6 or due to patient's choice). The two regimens of chemotherapy permitted were: (1) etoposide 100 mg/m^2^ intravenous day 1–3 and cisplatin 75 mg/m^2^ intravenous day 1, or (2) etoposide 100 mg/m^2^ intravenous day 1–3 and cisplatin 25 mg/m^2^ intravenous day 1–3. The use of granulocyte-colony stimulating factor during chemotherapy was permitted.^15^

No later than 6 weeks after the last cycle of chemotherapy, patients without evidence of progressive disease on chest X-ray or CT scan and with no clinical evidence of brain metastases were given prophylactic cranial irradiation.

### Translational research

Progress in treatment of SCLC has been hampered by limited understanding of the molecular biology of this disease. It is usually diagnosed on a small biopsy specimen or fine needle aspirate insufficient for detailed molecular studies. Consequently, existing SCLC tumour banks include relatively small series (<100 patients) of samples collected over many years from patients who are heterogeneous with respect to stage and treatment received. The CONVERT trial provides a unique opportunity to prospectively collect a large number of biospecimens from patients of uniform (limited) stage, who are exposed to the same chemotherapy, treated with one of two RT schedules and for whom there will be robust clinical outcome data. Although it will still be problematic to obtain large tumour biopsy specimens for many patients, advances in genomic and proteomic technology will enable studies to be performed on blood/serum samples in addition to small biopsy specimens.

All patients were asked to consent for an optional collection of tumour samples (paraffin embedded*)* and blood samples as part of the trial. Blood samples (for genomic and proteomic analysis) were collected at three time points: at baseline prior to any treatment, on day 22 of treatment and on completion of treatment. The sample collection schedule is shown in table 1.

**Table 1 BMJOPEN2015009849TB1:** Sample collection schedule

	Baseline	Day 22	End of treatment
Tissue block			
Serum	✓	✓	✓
Plasma	✓	✓	✓
Whole blood	✓		
CTC	✓		

CTC, circulating tumour cells.

### Data collection and management

Participating centres completed the following case report forms (CRFs):
Eligibility checklist prior to or at the time of randomisationPre-treatment and tumour assessment at baseline prior to cycle 1Treatment forms on day 1 of each chemotherapy cycle (cycles 1–4 or 6). The data collected included PS, protocol treatments received, toxicity and reasons for reduction/delay/omission of treatmentToxicity forms at the end of each cycle given, prior to next cycle and 30 days after completion of the last cycle of chemotherapyRadiotherapy worksheet during and after completion of RTPost treatment form 30 days after the last cycle of chemotherapyFollow-up forms at each follow-up visit starting at 3 months postcycle 4 (or 6) visit (continuing 3 monthly until 12 months and then 6 monthly thereafter)Serious adverse event (SAE) forms used to report all SAEsProgression/relapse/death forms to report the patient status.

Copies of all CRFs continue to be returned to the trials centre for statistical analysis. All forms are tracked and entered into a study-defined database for which consistency checking is programmed in. Data managers check for missing and invalid data using SQL queries and statistical programmes. Any queries raised are returned to the centres for correction or clarification.

On completion of the study, the data will be written onto compact disk and archived in a safe and secure location within the MAHSC-CTU. Paper copies of the CRF's will be retained at sites for at least 15 years following the last, patient entered or, if all are deceased may be archived off site. All paper data will be destroyed after 15 years on the approval of the chief investigator.

The trials centre staff are in regular contact with local centre personnel to check on progress and to help with any queries that may arise. Incoming forms are checked for completeness, consistency, timeliness and compliance with the protocol.

### Sample size calculation

It is considered that a survival benefit of 12% at 2 years (in favour of once-daily RT) would be clinically significant. Using Freedman's sample size calculation based on a two-arm trial, with a 5% significance level, two-sided test, 80% power and HR of 0.70, a 12% overall survival benefit at 2 years from 44% with the control arm to 56% in the experimental arm, required a total of 506 patients. The number of deaths required is 247. An additional 5% was added to allow for ineligible patients, giving a total of 532 patients required. An additional 15 patients were recruited (total of 547) to replace patients either randomised in error or for whom we were never able to obtain data.

### Statistical analysis plan

The analysis will be based on intention-to-treat principles (ITT). Patient data will be grouped by treatment arm according to the treatment assignments made via the MAHSC-CTU randomisation line. The primary data analysis is planned for January 2015.

The stratification factors include centre, PS (0–1 vs 2) and biochemical factors (eg, LDH, sodium, alkaline phosphatase). Comparison of data by centre will be scrutinised to identify any data inconsistencies, it will also be used to identify those centres planning to give either four or six cycles of chemotherapy. Analysis will be carried out to identify any differences between the two schedules. Other factors have been identified in previous studies to be prognostic factors and will be used to calculate the Manchester score, which gives three groupings of good, intermediate and poor prognosis; these scores will be used to compare OS and response rate.

The only planned interim analyses have been performed for the Independent Data Monitoring Committee (IDMC). Reports have been submitted to the IDMC on an annual basis starting 12 months after the first patient was randomised.

The following are the qualifications for analysis of time-to-event efficacy parameters:
All randomised patients will be included in the analysis of overall survival (OS) and local progression free survival (ITT).

OS is the time between date of randomisation and date of death of any cause. Survivors will be censored on the last date known to be alive. Local progression-free survival (local control) will be calculated from the date of randomisation to the date of first clinical evidence of progressive disease at the primary site, or death. Kaplan-Meier curves will be drawn for each treatment group. Overall survival and local progression-free survival will be compared using the Mantel-Cox version of the log rank test.
All randomised patients treated with at least one study dose of cisplatin and etoposide will be included in the comparison of proportions of grade 3 and 4 toxicities.

Toxicity will be assessed according to NCI Common Terminology Criteria for Adverse Events V.3.0. The proportion of patients experiencing a grade of 3 or above acute toxicity, including acute and/or late radiation morbidity, will be compared between the treatment groups using χ^2^ and Fisher Exact tests. Acute toxicity will be defined as toxicities occurring from commencement to 3 months after completion of treatment; late toxicity will be defined as toxicities occurring between 3 months and 2 years after completion of treatment.

All patients treated with at least one dose of cisplatin and etoposide will be evaluated for tumour response and included in the analysis of tumour response rates. Response will be assessed according to Response Evaluation Criteria In Solid Tumours (RECIST) criteria. The proportion of patients in each treatment group whose best response (up to approximately 28 days postcycle 4 or, if stopped prior to cycle 4, approximately 28 days after last chemotherapy cycle given) from randomisation is complete or partial will be compared using χ^2^ and Fisher Exact tests.

Safety analyses will be performed for all randomised patients treated with at least one dose of chemotherapy. Adverse effects will be summarised and compared between the two arms.

The relative chemotherapy and RT dose intensity (RDI) will be summarised by calculating the median, SD, IQR and range for patients in each randomised treatment group. The RDI will be compared between the treatment groups by using the Wilcoxon Rank Sum test.

A detailed description of patient disposition will include a summary of the following:
All patients entered and enrolled: overall, by treatment arm and by countryReasons for patients entered but not enrolledAll enrolled patients treated with study drug, by treatment armReasons patients enrolled but not treated with study drugReasons patients discontinued study drug treatmentAll important protocol violations.

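### The analysis section names stratification factors that differ from the minimisation factors, and ties the survival test to none of them

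*Protocol article*

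**What the plan says.** On allocation, the Randomisation section states: "The allocation method used was minimisation with a random element". It then names the factors: "The factors controlled for in the allocation were institution, planned number of cycles (4 or 6) and PS (0/1 or 2". Biochemistry appears in that section only as part of the check made before allocation: "including recording of LDH, sodium and alkaline phosphatase results".

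The Statistical analysis plan section states: "The stratification factors include centre, PS (0–1 vs 2) and biochemical factors (eg, LDH, sodium, alkaline phosphatase". Planned cycles is not in this list. The following sentence says of the centre data that "it will also be used to identify those centres planning to give either four or six cycles of chemotherapy". The Interventions section explains the link, since cycle number was mainly a centre policy: "Centres were given the choice to stop chemotherapy after four cycles or to continue it up to six cycles".

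The test for the primary endpoint is given as: "Overall survival and local progression-free survival will be compared using the Mantel-Cox version of the log rank test". No strata or covariates are named with it. The same section also plans to compare overall survival (OS) by Manchester score group, but does not connect that to the primary test.

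**The concern.** The factors that constrained the allocation should be identifiable from the protocol, because they determine which analysis matches the design. Here two sections disagree. One factor group (LDH, sodium, alkaline phosphatase) is called a stratification factor although the Randomisation section does not list it as controlled. One controlled factor (planned cycles) is left out of the list. The section on changes to the protocol reports nothing significant after the start, so no stated amendment explains the difference.

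Two things are at stake. First, an analyst who takes the analysis section literally could build strata that the trial never balanced on. Second, minimisation on prognostic factors makes the arms more alike than simple randomisation would. A test that ignores those factors then tends to use too large a variance, which makes it conservative and can cost power. In a non-blinded trial, the choice between a plain and a stratified primary test should also not be left open to interpretation.

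**Working it through.** **1. The plan's own figure.** Inputs from the Sample size calculation section: HR 0.70, two-sided 5%, 80% power, 2-year survival 44% against 56%.

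- Freedman deaths: (1.960 + 0.842)² × ((1 + 0.70)/(1 − 0.70))² = 7.849 × 32.11 = 252.04, so 253.
- Patients: 2 × 252.04 / (2 − 0.44 − 0.44^0.70) = 504.07 / 0.9971 = 505.5, so 506 as stated.
- The stated 247 deaths is the Schoenfeld figure: 4 × 7.849 / (ln 0.70)² = 246.8. It is within 3% of Freedman's.
- 506 × 1.05 = 531.3, so 532 as stated.

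The design figures therefore reproduce. Neither formula contains a stratification factor.

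**2. The two lists side by side.**

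| Factor | Randomisation | Statistical analysis plan |
|---|---|---|
| Institution/centre | yes | yes |
| PS (0–1 vs 2) | yes | yes |
| Planned cycles (4 or 6) | yes | not listed; identified through centre |
| LDH, sodium, alkaline phosphatase | recorded only | yes |

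Factors named with the OS log-rank test: none.

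**3. Size of the consequence, by simulation.** All runs used 547 patients, 74 centres and minimisation. These assumptions are not in the documents: a minimisation probability of 0.8 and the strength of every prognostic effect. Set B also assumes 5% PS 2, half of centres planning six cycles, and 30% of patients with an adverse biochemical factor.

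*Set A* (HR 0.706, censoring at 24 months, about 275 deaths, about 4,500 to 4,900 trials per scenario; for example raised LDH HR 1.35 to 1.73, PS 2 HR 1.5 to 2.0):

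- Unadjusted type I error is 4.7% to 4.8%. The Monte Carlo SE is √(0.05 × 0.95/4700) = 0.32 points, so this cannot be distinguished from 5%.
- Power with strong factors is 78.0% unadjusted, 78.4% with cycles and PS, and 80.4% with biochemistry added.
- Power with weak factors is 79.9%, 79.9% and 80.2%.

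*Set B* (HR 0.70, longer follow-up and more than 247 deaths; 4,000 null runs and 1,000 power runs per scenario). Moderate and strong mean a centre log-hazard SD of 0.3 and 0.6, PS 2 HR 1.5 and 2, cycles HR 1.3 and 1.5, and biochemistry HR 1.5 and 2:

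| Prognostic strength | Measure | Unstratified | Cycles × PS | Centre |
|---|---|---|---|---|
| None | type I error | 5.0% | 4.9% | 5.3% |
| Moderate | type I error | 4.4% | 4.6% | 5.0% |
| Strong | type I error | 3.6% | 3.9% | 4.8% |
| None | power | 94.4% | 94.3% | 88.6% |
| Moderate | power | 91.2% | 91.4% | 88.9% |
| Strong | power | 83.4% | 84.7% | 86.1% |

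With 4,000 runs the SE at 5% is 0.34 points, so only the strong scenario shows clear conservatism in the unstratified test: (5.0 − 3.55)/0.34 = 4.3 SE.

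**4. Reading the results.** Stratifying by cycles × PS changes power by −0.1, +0.2 and +1.3 points in set B, and by 0 and +0.4 in set A. Adding biochemistry in set A takes the gain over the unadjusted test to 80.4 − 78.0 = 2.4 points at most. Stratifying by centre ranges from 88.6 − 94.4 = −5.8 to 86.1 − 83.4 = +2.7 points. With 547/74 = 7.4 patients per centre on average, it pays only if centre effects are large.

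**The case against.** Several points for the plan stand.

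- The list is introduced with a word that does not claim completeness, cycle number is largely a centre policy, and the next sentence recovers it through centre. Planned cycles is handled loosely rather than discarded. This does not excuse listing biochemistry, which the Randomisation section does not include among the controlled factors.
- The article never calls the log-rank test unstratified. It is a condensed account, and a separate analysis plan may specify strata and an effect estimate. Their absence here is not a fault. The contradiction between the two sections does not depend on that silence.
- Prognostic information is planned for OS through the Manchester score, so it is not ignored altogether.
- The gain from biochemistry is ordinary covariate adjustment and has nothing to do with matching the allocation.

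A reader might infer that the listed factors are to be crossed as strata. That would give 74 × 2 × 4 = 592 cells for 547 patients, since eligibility allows at most one adverse biochemical factor. In a further simulation (HR 0.706, 24-month censoring, 1,500 runs per scenario), power under such a scheme fell to 65% to 66%, against 78% to 82% for the plain test. The article never proposes this stratification, so the figure is a reason to clarify the wording and not a defect of the stated test.

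**Conclusion.** The two sections contradict each other on the stratification factors, and the article does not say what role those factors play in the primary comparison. This follows from the text alone.

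A reader might go further and conclude that the primary test is invalid or seriously underpowered because it does not match the allocation. The documents do not support that. An unstratified log-rank after minimisation does not inflate type I error. It is at most mildly conservative (3.6% in the most strongly prognostic scenario tried, close to 5% otherwise), and the power at stake is about 0 to 2 points. These sizes rest on assumed prognostic effects, PS 2 frequency and minimisation probability.

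Stratifying by cycles and PS recovers only a little of the conservatism (3.6% to 3.9% in the strong case), because much of the balance comes from institution. The change is a worthwhile and nearly free improvement, and not a condition for a valid analysis.

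**What to change.** - Correct the Statistical analysis plan section so that the allocation factors are institution, planned cycles (4 or 6) and PS (0–1 vs 2), and describe LDH, sodium and alkaline phosphatase as prognostic covariates recorded before randomisation.
- State that the primary OS log-rank test is stratified by planned cycles and PS. Say explicitly that institution is not a stratum because 74 centres are too sparse.
- Report the HR and 95% CI from a Cox model with the same strata, so that test and interval come from one coherent analysis.
- Give two sensitivity analyses: the unstratified log-rank, and a Cox model further adjusted for LDH, sodium and alkaline phosphatase.
- Apply the same to local progression-free survival.

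The cost is a few sentences and a few lines of code, because every variable was recorded by the time of randomisation. Timing is the real constraint. The trial is non-blinded, the primary analysis was planned for January 2015, and the article is dated January 2016. The choice must be fixed before comparative data are seen. If they have been seen, keep the primary test as already specified and report the stratified analysis as supportive. The factor list should be corrected in either case.
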